## TRIAL SCHEMA

[figure not shown]

**TABLE 1- SCHEDULE OF OBSERVATIONS AND PROCEDURES**

| Domain / data type                | CRF/Assessment questionnaire                                                 | Assessor/person completing form | 12-16 Participants |                      | Week                  |   |   |   |             |             |
|-----------------------------------|------------------------------------------------------------------------------|---------------------------------|--------------------|----------------------|-----------------------|---|---|---|-------------|-------------|
|                                   |                                                                              |                                 | Screening          | Baseline & Randomise | Intervention delivery |   |   |   | Follow up   |             |
|                                   |                                                                              |                                 |                    |                      | 1                     | 2 | 3 | 4 | 6           | 26          |
| Window                            |                                                                              |                                 |                    |                      |                       |   |   |   | +/- 2 weeks | +/- 4 weeks |
| Reply slip / Contact details      | Letter of invitation / Contact information form                              | Participant                     | X                  |                      |                       |   |   |   |             |             |
| Eligibility screening             | Baseline Checklist CRF                                                       | Research Nurse (RN)             | X                  |                      |                       |   |   |   |             |             |
| Route of recruitment              | Screening log                                                                | RN                              | X                  |                      |                       |   |   |   |             |             |
| Reason not interested             | Screening log                                                                | RN                              | X                  |                      |                       |   |   |   |             |             |
| Re-Eligibility Screening Check    | Baseline Checklist CRF                                                       | RN                              |                    | X                    |                       |   |   |   |             |             |
| Demographics          | Baseline CRF                                                                 | Participant                     |                    | X                    |                       |   |   |   |             |             |
| Clinical information  | Baseline CRF                                                                 | RN/ Participant                 | x                  |                      |                       |   |   |   |             |             |
| Consent                           | Consent form                                                                 | Participant/RN                  |                    | X                    |                       |   |   |   |             |             |
| Intervention allocation           | Randomisation CRF                                                            | CTU/Statistician                |                    | X                    |                       |   |   |   |             |             |
| Hot flushes and night sweats      | - HFNS Rating Scale (and HFNS Subscale)
- HFNS Belief and Behaviour Scale | Participant                     |                    | X                    |                       |   |   |   | X           | X           |

| Domain / data type                                                                             | CRF/Assessment questionnaire                         | Assessor/person completing form             | 12-16 Participants |                      | Week                  |   |   |   |             |             |
|------------------------------------------------------------------------------------------------|------------------------------------------------------|---------------------------------------------|--------------------|----------------------|-----------------------|---|---|---|-------------|-------------|
|                                                                                                |                                                      |                                             | Screening          | Baseline & Randomise | Intervention delivery |   |   |   | Follow up   |             |
|                                                                                                |                                                      |                                             |                    |                      | 1                     | 2 | 3 | 4 | 6           | 26          |
| Window                                                                                         |                                                      |                                             |                    |                      |                       |   |   |   | +/- 2 weeks | +/- 4 weeks |
| Health-related QoL                                                                             | - EORTC QLQ-C30                                      | Participant                                 |                    | X                    |                       |   |   |   | X           | X           |
| Anxiety, depression and mood                                                                   | - GAD7
- PHQ9
- WSAS                           | Participant                                 |                    | X                    |                       |   |   |   | X           | X           |
| Sleep                                                                                          | PSQI (item 6 only)                                   | Participant                                 |                    | X                    |                       |   |   |   | X           | X           |
| Compliance to ADT                                                                              | ADT Compliance Questionnaire                         | Participant                                 |                    | X                    |                       |   |   |   | X           | X           |
| CNS training                                                                                   | CNS Training Evaluation Questionnaire                | CNS                                         | X                  |                      |                       |   |   |   |             |             |
| Attendance                                                                                     | Attendance log                                       | CNS                                         |                    |                      | X                     | X | X | X |             |             |
| Reflections and questions post CBT group workshops
Number of length of supervision sessions | Supervision notes                                    | CNS                                         |                    |                      | X                     | X | X | X |             |             |
| Fidelity: pre and post intervention workshop delivery                                          | Audio recordings of virtual pre/post group workshops | CNS to record all pre/ post group workshops |                    |                      | X                     |   |   | X |             |             |
| Adherence: Self-Guided CBT Booklet                                                             | Patient Evaluation Questionnaire                     | Participant (intervention arm only)         |                    |                      |                       |   |   | X |             |             |

| Domain / data type                                    | CRF/Assessment questionnaire           | Assessor/person completing form                          | 12-16 Participants |                      | Week                                     |   |   |   |             |             |
|-------------------------------------------------------|----------------------------------------|----------------------------------------------------------|--------------------|----------------------|------------------------------------------|---|---|---|-------------|-------------|
|                                                       |                                        |                                                          | Screening          | Baseline & Randomise | Intervention delivery                    |   |   |   | Follow up   |             |
|                                                       |                                        |                                                          |                    |                      | 1                                        | 2 | 3 | 4 | 6           | 26          |
| Window                                                |                                        |                                                          |                    |                      |                                          |   |   |   | +/- 2 weeks | +/- 4 weeks |
| engagement & Lifestyle changes                        |                                        |                                                          |                    |                      |                                          |   |   |   |             |             |
| Fidelity: pre and post intervention workshop delivery | Fidelity Checklist                     | Independent person                                       |                    |                      | 2 recordings per site randomly allocated |   |   |   |             |             |
| Resource usage                                        | Participant Resource use Questionnaire | Participant                                              |                    |                      |                                          |   |   |   | X           | X           |
| Management of HFNS                                    | Participant resource use Questionnaire | Participant                                              |                    |                      |                                          |   |   |   | X           | X           |
| Clinic costs                                          | Nurse logs                             | CNS                                                      |                    | X                    | X                                        | X | X | X |             |             |
| Nurse time                                            | Nurse logs                             | CNS                                                      |                    | X                    | X                                        | X | X | X |             |             |
| Training costs                                        | Nurse logs                             | CNS                                                      |                    | X                    |                                          |   |   |   |             |             |
| QoL                                                   | - EORTC QLQ-C30
- EORTC QLQ-PR-25   | Participant                                              |                    | X                    |                                          |   |   |   | X           | X           |
| Evaluation of intervention                            | Patient Evaluation Questionnaire       | Participant (intervention arm only)                      |                    |                      |                                          |   |   | X |             |             |
| Experiences of participating in the CBT group         | (Optional) Participant interviews.     | Participant (Intervention Arm only) / SCTU Research Team |                    |                      |                                          |   |   | X |             |             |

| Domain / data type                            | CRF/Assessment questionnaire        | Assessor/person completing form   | 12-16 Participants |                      | Week                  |   |   |   |             |             |
|-----------------------------------------------|-------------------------------------|-----------------------------------|--------------------|----------------------|-----------------------|---|---|---|-------------|-------------|
|                                               |                                     |                                   | Screening          | Baseline & Randomise | Intervention delivery |   |   |   | Follow up   |             |
|                                               |                                     |                                   |                    |                      | 1                     | 2 | 3 | 4 | 6           | 26          |
| Window                                        |                                     |                                   |                    |                      |                       |   |   |   | +/- 2 weeks | +/- 4 weeks |
| Implementation and impact on current services | NoMad Questionnaire/ CNS interviews | CNS Team member (x2)              | X                  |                      |                       |   |   |   |             | X           |
| Implementation of program                     | Managers interviews                 | Managers/ SCTU Research Team      |                    |                      |                       |   |   |   |             | X           |
|                                               | Medical Staff interviews            | Medical Staff/ SCTU Research Team |                    |                      |                       |   |   |   |             | X           |
| SAE Collection                                |                                     |                                   |                    |                      |                       |   |   |   | X           | X           |

 See baseline section 5.1 for the breakdown of Demographic and Clinical data to be collected from participants.

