#### **4.1.4 Completion of Baseline Questionnaires**

Baseline Questionnaires (containing Demographic questions, HFNS Rating Scale, HFNS Sub Scale, HFNS Belief and Behaviour scale, EORTC-QLQ-C30, , GAD7, PHQ9, WSAS and PSQI item 6) will be provided (in person or via mail) to all eligible men following their screening review. The site research team will complete the clinical Baseline form using patient medical notes and may contact the patient (telephone or face to face) to complete some sections of this form.

Where Baseline Questionnaires have not been returned to the research team within 7-10 days of the site trial team providing or posting out, the site trial team will call the patient and will arrange to collect the measures over the telephone. They may also collect incomplete measures with the patient over the telephone.

The site trial team may use a range of methods to communicate with patients such as video conferencing, emails, text and telephone calls.

Randomisation will be undertaken (see section 4.5) once all (12-16) men have completed their Baseline Questionnaires.

For further information on recruitment, screening and baseline procedures please refer to the MANCAN2 Patient Flow document.

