#### **2) Participants**

Data will be collected on all participants about other actions that they may be taking to manage their HFNS, including yoga, acupuncture or other behavioural activities (see section 7.4). Collection of such information from each participant will be through questionnaire sent by mail at 6 weeks and 6 months. QoL will be measured by EORTC-QLQ-C30 and will be collected at baseline, 6 weeks and 6 months.

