### **7.3 PRIMARY AND SECONDARY ANALYSES**

The primary outcome measure, HFNS Rating Scale compared to baseline, will be compared between the CBT intervention + TAU arms at 6 months post randomisation. Difference in HFNS Rating Scale between the two groups will be analysed using a linear mixed model, adjusting for baseline HFNS Rating Scale and stratification factors. Therapy group will be included in the model as a random effect. Interpretation of the effect of the intervention will be based on the regression coefficient for group and corresponding 95% confidence interval. Secondary outcomes at 6 weeks and 6 months post-randomisation will be analysed similarly, accounting for stratification factors and clustering.

Analyses will be based on a modified intention-to-treat sample (i.e. excluding participants not contributing data). This will be supported by an analysis that deals with missing data should missingness lead to >10% of the sample being excluded. Methods may involve either multiple imputation using chained equations, or full information maximum likelihood.

MANCAN2 will be analysed according to the principles of the International Conference on Harmonisation E9 guidelines and reported using Consolidated Standards of Reporting Trials (CONSORT). A full statistical analysis plan (SAP) will be developed prior to the final analysis.

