### **7.4 HEALTH ECONOMIC ANALYSES**

The economic analysis will take an NHS perspective to estimate both cost effectiveness (£ per change in HFRS) and cost utility (Incremental £/QALY) as well as a budget impact. QALYs will be estimated from EORTC using the SCHARR algorithm (<https://www.sheffield.ac.uk/scharr/sections/heds/mvh/cancer>).

Costs will include that of the intervention and on any changes in use of NHS services. As the intervention cost might differ between that in the trial and in routine practice, we will take two approaches, one detailing changes in CNS team total time allocations in each arm during the trial, and another collecting data on views of both the CNS team and managers on the extent to which the intervention could be incorporated into standard practice (and under what circumstances such as being included in training and in guidelines). While both these costs will be reported, the latter would be more relevant in estimating budget impact if implemented in routine practice. The cost of changes in service use will be based on a customised resource use patient questionnaire at 6 weeks and 6 months.

Estimates of both cost and QALY increments will be estimated for each patient and incorporated into the planned statistical analyses described above. If a clinically relevant gain in the primary outcome is found to be statistically significant, more detailed economic modelling will be carried out, to explore uncertainty and to extend the time frame beyond that of the trial. This will build on the recent cost effectiveness modelling for similar interventions for hot flushes in breast cancer.[39]

All relevant resource items identified will be costed using published national cost data (British National Formulary and Personal Social Services Research Unit, and NHS reference cost). Accumulated costs and QALYs per patient will be estimated by means of area under the curve. Where appropriate we will estimate incremental cost-effectiveness ratios (ICERs). We will estimate mean values and 95% percentiles using non-parametric bootstrapping. We will produce cost-effectiveness acceptability curves (CEACs) to illustrate the uncertainty of such estimates. Major assumptions made in the costing and QALYs will be tested by means of sensitivity analyses.

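### Resource use is never measured before randomisation, so the change in NHS use costed in 7.4 can only be a between-arm difference without baseline-cost adjustment, at a loss of precision

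*Protocol*

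**What the plan says.** Section 7.4 of the protocol sets out what is costed: "Costs will include that of the intervention and on any changes in use of NHS services". It then names the source: "The cost of changes in service use will be based on a customised resource use patient questionnaire at 6 weeks and 6 months". Section 3.1.6 says the same.

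The schedule agrees with those two time points. In Table 1 the row "Participant Resource use Questionnaire | Participant" (Resource usage), and the Management of HFNS row that uses the same form, are marked at weeks 6 and 26 and are blank under Baseline. Section 5.3.3, under Participants, says of other actions taken to manage HFNS: "Collection of such information from each participant will be through questionnaire sent by mail at 6 weeks and 6 months".

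The baseline pack in 4.1.4 lists the HFNS scales and then "HFNS Belief and Behaviour scale, EORTC-QLQ-C30, , GAD7, PHQ9, WSAS and PSQI item 6"; no resource-use form is among them. Section 5.1 adds a yes/no list of current HFNS treatments, with no visits, quantities or costs. The paragraph on concomitant medications after 4.3 says that medication use will be recorded, but names no form, time point or service use.

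On analysis, 7.4 states: "Estimates of both cost and QALY increments will be estimated for each patient and incorporated into the planned statistical analyses described above". The analyses above it are those of 7.3, where the primary model is described as "adjusting for baseline HFNS Rating Scale and stratification factors", with secondary outcomes handled similarly. Section 5.3.3 bases cost-effectiveness on incremental differences between the arms and makes the full evaluation conditional on an improvement of at least 1.5 points in the HFNS score.

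**The concern.** Read naturally, a change in service use needs a before and an after, and here there is no before. The other inputs to the economic analysis do have a baseline entry in Table 1: the HFNS Rating Scale and the QLQ-C30, which form the effect side of the two ratios, and the nurse logs of time and clinic cost. Patient service use is the exception.

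A later analysis plan can choose a model, but it cannot recover data that were not collected. Two things are at stake. First, the quantity in 7.4 is left open to two readings, only one of which the data can supply. Second, a man's earlier use of services probably predicts his use during the trial, and without it the cost comparison gives up precision. The sample size in 7.2 was set for the HFNS rating and not for cost, so there is no stated reserve of precision on the cost side.

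**Working it through.** The protocol gives no cost figure, cost SD or precision target, so there is no stated number to reproduce. The check has two parts.

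**1. What the scheduled data can supply**

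- *Change from pre-randomisation use:* needs service use at baseline. Table 1, 4.1.4 and 5.1 provide none. Not obtainable.
- *Adjustment of a man's cost for his own earlier cost:* needs the same data. Not obtainable.
- *Between-arm difference in follow-up cost (5.3.3):* needs the week-6 and week-26 forms only. Obtainable, provided their recall periods cover the interval; the protocol does not state them.
- *The model named in 7.3:* needs baseline HFNS score and the stratification factors, all of which are collected. It can be fitted to costs.

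**2. What the missing baseline costs in precision**

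Inputs: 111 men analysed (7.2, which is 150 × (1 − 0.26)), so about 55 per arm; 1:1 allocation (4.5); r, the correlation between earlier and trial cost, *assumed* to be 0.3, 0.5 or 0.7. Clustering is ignored and the relation is taken as linear.

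The standard error with baseline adjustment, divided by that from follow-up alone, is √(1 − r²). Its inverse gives the relative width of the unadjusted interval. The number of men with adjustment who would give the same precision as 111 without it is 111 × (1 − r²).

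| r (assumed) | √(1 − r²) | Interval width without baseline, relative to with | 111 × (1 − r²) |
|---|---|---|---|
| 0.3 | √0.91 = 0.954 | 1.048 (about 5% wider) | 101 |
| 0.5 | √0.75 = 0.866 | 1.155 (about 15% wider) | 83 |
| 0.7 | √0.51 = 0.714 | 1.400 (40% wider) | 57 |

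The percentages do not depend on the sample size; only the last column does.

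**Is there bias?** With 55 per arm, the chance difference between arms in earlier cost has a standard error of √(2/55) = 0.19 SD, so its 95% range is ±1.96 × 0.19 = ±0.37 SD. A simulation of 20,000 trials with no true cost difference (normally distributed costs) tested whether this distorts the comparison from follow-up alone. The mean estimated difference was below 0.001 SD for every r, and the 95% interval covered the truth in 94.5% to 94.9% of trials. The SD of the estimate fell from 0.193 to 0.184 (r = 0.3), from 0.191 to 0.165 (r = 0.5) and from 0.191 to 0.136 (r = 0.7) after adjustment, in line with the formula. The imbalance is random error that the unadjusted interval already includes.

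**Adjust or subtract?** If baseline cost were available and had the same SD as trial cost, a simple change score would have √(2(1 − r)) times the follow-up-only standard error: 1.18, 1.00 and 0.77 for the three values of r. Subtraction is thus worse than no baseline at r = 0.3, no better at r = 0.5, and at each value less precise than adjustment. The baseline is useful as a covariate.

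**The case against.** The strongest reply is that nothing the protocol defines has been lost. Section 5.3.3 rests cost-effectiveness on the difference between arms, and change in NHS use can be read as what the intervention changes relative to usual care. All sections agree on two follow-up time points, so the schedule does not contradict itself. Economic methods are also deferred to a combined statistical and health economic plan.

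Most of this stands, and it rules out three stronger readings.

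- A reader might infer that the cost result cannot be computed at all. It can: the between-arm contrast needs only follow-up data.
- A reader might infer from 7.4's reference back to 7.3 that the planned cost model cannot be fitted for want of baseline cost. Section 7.3 names only the baseline HFNS score, which is collected; for secondary outcomes it mentions stratification factors and clustering. Baseline cost is never named.
- A reader might infer that chance differences in earlier NHS use bias the cost result. Under 1:1 randomisation they do not, and disease status, one obvious driver of use, is already a stratification factor (7.1).

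What does not stand is leaving the matter to the analysis plan. That plan can settle the meaning of change, but it cannot supply a baseline value. The wording of 7.4 also does not by itself point to the between-arm reading: the same paragraph speaks of changes in staff time within each arm.

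**Conclusion.** The point holds as a limited one. No pre-randomisation service use is collected, so a change from baseline and an adjustment for earlier cost are not obtainable, and 7.4 does not say which meaning of change it intends. The between-arm cost difference remains computable and unbiased, with valid intervals.

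The cost is precision: intervals about 5%, 15% or 40% wider than they could be. Those figures rest entirely on assumed correlations of 0.3, 0.5 and 0.7; a weaker correlation would make the loss negligible. Real costs are usually skewed, so the simulation supports the direction and rough size and not exact coverage.

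The primary HFNS result is unaffected, and the full economic evaluation is secondary and runs only if the intervention proves effective. This is a cheap improvement, not an error that invalidates a planned analysis.

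**What to change.** - **Table 1:** add a Baseline X to the Resource usage and Management of HFNS rows.
- **Section 4.1.4:** add the same Participant Resource Use Questionnaire to the baseline pack.
- **Section 7.4 (and the matching text in 3.1.6):** state that change in service-use cost means the between-arm difference in follow-up cost per participant, adjusted for baseline cost (where collected) and the stratification factors.

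The cost is one existing form added to a pack that is already provided and followed up by telephone, a few more minutes per man at baseline, and a protocol amendment. Treatment, randomisation and the primary endpoint do not change. Men already randomised will have no baseline value, so the analysis plan should say how they are kept in the adjusted comparison.

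If recruitment is too far advanced for this to be useful, the minimum is a text change: define change in 7.4 as the between-arm difference in follow-up cost, and state that no baseline cost exists.
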